### Adverse events and termination of trial

2.6

For safety reasons, we will record all unexpected reactions related to the study treatment with detailed description, including time of occurrence, duration of symptoms, severity of symptoms, management measures, time when adverse reactions disappear and classification of causality. The investigator will document and manage all adverse events, whether or not they are related to the study treatment. If more than 25% of patients stop the intervention due to adverse events, the superior physician will make the decision to terminate the trial. The case report form (CRFs) will be used for data collection to record demographics, assessments, and reasons for patient withdrawal. At the end of the study, the investigators will submit the CRFs form to the data Management Committee.

### Data collection and management

2.7

The data of this study were collected by two assistants and entered into a pre-designed table. The relevant information and data of this study will be collected, shared, and stored in a separate repository to protect the confidentiality before, during and after the test. People outside the research group have no access to the relevant information. Without the written permission of the participants, the research information of the participants will not be published outside the study.

### Statistical analysis

2.8

The data were analyzed by SPSS.22 software package, the hypothesis test was two-tailed test, and the α level was set to *P* < .05. The measurement data in accordance with normal distribution and homogeneity of variance are tested by independent sample *T* test, while those inconformable are tested by Mann–Whitney *U* test.

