#### Participants source and sample size estimation

2.2.1

We will include patients through pre-hospital recruitment and screening of inpatients. After qualification assessment, patients will be informed of the protocol and purpose of the trial, and will be included in the study only after consenting to the study and signing an informed consent form.

Sample size estimation will be based on post-treatment Total nasal symptom score.^[19]^ According to the pre-experiment results, the real EAP group was 2.82 ± 1.48, and the Sham EAP group was 3.47 ± 1.57, α = 0.05, β = 0.2, and 107 samples were needed in each group according to the calculation by PASS15.0 software. Consider a drop-out rate of no more than 20%, with 134 cases in each group.

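### Section 2.8 lets normality and variance checks choose between the t test and Mann–Whitney, so the primary test and estimand are not fixed, and Mann–Whitney is the wrong fallback for unequal variances

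*Protocol article*

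**What the plan says.** Section 2.8 (Statistical analysis) is the only place in the protocol article that names a test. Its first branch reads "The measurement data in accordance with normal distribution and homogeneity of variance are tested by independent sample" t test. Its second branch covers all remaining measurement data: "while those inconformable are tested by Mann–Whitney" U test. Testing is two-sided at the 5% level. The section does not exempt the primary outcome from this rule, and it offers no unequal-variance t test.

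Section 2.2.1 plans the trial on a different footing. It says "Sample size estimation will be based on post-treatment Total nasal symptom score", gives the pilot results as means and SDs ("the real EAP group was 2.82 ± 1.48, and the Sham EAP group was 3.47 ± 1.57"), and concludes: "α = 0.05, β = 0.2, and 107 samples were needed in each group according to the calculation by PASS15.0 software". With 20% dropout this becomes 134 per group.

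**The concern.** Two things in this rule do not fit the rest of the plan.

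First, the sample size is built to detect a difference in mean symptom score. Under section 2.8 the primary p-value may come instead from a rank test, which asks whether a score from one arm tends to exceed a score from the other. Features of the observed data decide which question is answered. The answer can differ between the primary score, the quality-of-life score and the individual visits.

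Second, the rule treats unequal variance as a reason to use Mann–Whitney. When spread or shape differs between arms, that test does not test equality of means. It can reject when the means are equal, and its p-value need not match the mean difference that was powered. Welch's t test handles unequal variances directly and still addresses the means.

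**Working it through.** **The plan's own figure.** Inputs from section 2.2.1: means 2.82 and 3.47, SDs 1.48 and 1.57, α = 0.05 two-sided, power 80%.

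- Difference: 3.47 − 2.82 = 0.65.
- Pooled SD: √[(1.48² + 1.57²)/2] = √2.3277 = 1.526. SD ratio: 1.57/1.48 = 1.06.
- n per group = 2(1.960 + 0.842)² × 1.526²/0.65² = 86.5, so 87 (88 with the exact t distribution).

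The stated 107 is therefore not reproduced; at 107 per group the t test has about 87% power. The dropout step does reproduce: 107/0.80 = 133.75, so 134. The gap between 88 and 107 is a separate matter. What matters here is that the inputs are means and SDs, so the planned quantity is a mean difference.

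**What the rule does in each case.**

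| Normal? | Equal variances? | Test under section 2.8 | Tests equal means? |
|---|---|---|---|
| yes | yes | t test | yes |
| yes | no | Mann–Whitney | not in general; Welch would |
| no | yes | Mann–Whitney | only if the shapes match |
| no | no | Mann–Whitney | no |

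**Simulation of the rule.** There were 107 per arm, equal true means, and 2,000 to 4,000 runs per scenario. The article names no check or threshold, so Shapiro–Wilk in each arm plus Levene, each at 0.05, is assumed. If all checks pass the t test is used, otherwise Mann–Whitney. Monte Carlo standard error at a true 5%: √(0.05 × 0.95/4000) = 0.34 points for 4,000 runs, 0.49 points for 2,000. Ranges come from repeat runs.

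| Scores, equal means | SDs | Rule rejects | Welch rejects | Sent to Mann–Whitney |
|---|---|---|---|---|
| Normal, mean 3.47 | 1.48 / 1.57 | 5.4% | 5.3% | 17% |
| Gamma, mean 3.47 | 1.48 / 1.57 | 4.7% | 4.6% | 99% |
| Gamma, mean 3.47, rounded | 1.48 / 1.57 | 5.0% | 4.7% | 100% |
| Normal, mean 3.47 | 1.5 / 3.0 | 6.0% | 4.8% | 100% |
| Gamma, mean 3 | 1.5 / 1.8 | 6.7–7.4% | 4.5–4.7% | – |
| Gamma, mean 3 | 1.5 / 2.2 | 19.8–20.0% | 4.9–5.2% | – |
| Gamma, mean 3.47 | 1.5 / 2.25 | 17.8% | 4.7% | 100% |
| Gamma, mean 3.47, rounded | 1.5 / 2.25 | 16.8% | 5.2% | 100% |
| Gamma, mean 3.47 | 1.5 / 3.0 | 50.4% | 5.0% | 100% |

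Only the SDs in the first three rows come from the protocol. The shapes, and every wider SD ratio, are assumptions. The inflation needs skew and unequal spread together: normal scores with a twofold SD ratio reach only 6.0%. It also grows with skew. For a gamma score skewness is 2 × SD/mean, so SD 2.2 at mean 3 (1.47) is more skewed than SD 2.25 at mean 3.47 (1.30), which is why the former gives the higher rate.

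**Power at the planning values.** With rounded normal scores the rule has 85–86% against 87% for the t test. With gamma scores the rule has 90–91% against 86–88% for a comparison of means.

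**The case against.** Several arguments limit this point, and most of them stand.

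- A reader might infer that the trial's type I error will be far above 5%. The documents do not support that. The only SDs given are 1.48 and 1.57, and there the rule performs like Welch's test. If real and sham ear acupuncture have identical effects, the two distributions are the same and Mann–Whitney is valid: with identical arms the rule rejected in 4.7% (gamma), 4.8% (normal) and 5.0% (rounded) of runs. The inflation concerns only equal means with different distributions.
- A reader might infer that the primary test will almost always be Mann–Whitney. That depends on an unnamed normality check and on how coarse the score is, and the article gives no scoring range. In simulation the switch rate was 98–100% for whole-number scores with SD 1.6 to 2.1, about 50% with SD 3, and about 14–17% for continuous normal scores.
- A reader might call this post hoc selection. The rule is written in advance and turns on shape and spread, not on which test gives the smaller p-value. That the checks are run on the trial's own data is the natural reading, but it is inferred.
- Power is not a serious cost, and with skewed scores of similar spread the rank test gains a little.

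None of this removes the core. The switch is stated text and not a detail left to an unseen analysis plan, and a rule written in advance can still leave the primary hypothesis open.

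**Conclusion.** The point holds in a limited form. Section 2.8 does not fix the primary test or estimand, whereas section 2.2.1 fixes a difference in means; and it sends unequal-variance data to a test that does not then assess equal means. Neither statement depends on a simulation assumption.

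The numerical consequence is conditional. At the documented SDs there is no material inflation and only a small power difference, in either direction. Error of about 7% to 20% needs assumed skew, equal means and SD ratios of 1.2 to about 1.5 (1.8/1.5 and 2.2/1.5), against the pilot ratio of 1.06. Even in the most favourable case, normal data at the pilot SDs, chance sends about one trial in six to the other test under the assumed checks. This is a defect worth correcting because the correction is cheap; it does not show that the trial would give a wrong answer.

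**What to change.** Delete the assumption-dependent switch from section 2.8 and name one primary analysis in advance: the between-group difference in mean total nasal symptom score with its 95% confidence interval, from a linear model adjusted for the baseline score with heteroscedasticity-robust standard errors. With baseline in the model the treatment estimate is the same, apart from sign, whether the outcome is entered as the decrease or as the post-treatment score. If an unadjusted comparison is preferred, Welch's t test is enough to cure the defect. Keep Mann–Whitney only as a labelled sensitivity analysis.

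This takes one or two sentences and no extra data. The small downside is that a rank test can be slightly more powerful if scores turn out skewed with similar spreads.

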### Study monitoring

2.9

The hospital clinical trial management department will be responsible for monitoring the progress of this study, and the organization will not be involved in the study at all, and there will be no conflict of interest. On-site monitoring meetings are held before and after the start of the study and quarterly to monitor the progress of the study and to ensure that it is carried out in accordance with established protocols, good clinical practice guidelines and applicable regulatory requirements. Although a separate data monitoring committee will not be established, the hospital clinical trial management department will perform this function by regularly monitoring this clinical trial to ensure scientific validity, scientific integrity, and data accuracy.

## Discussion

3

Allergic rhinitis is often induced by weather changes, pollen, animal hair, diet and other allergic factors, the main clinical manifestations are continuous episodes of paroxysmal sneezing, a large number of watery snot, nasal congestion and itching, and some patients have decreased sense of smell, affecting the quality of life.^[22]^ AR is an allergic reaction mediated by IgE under the chemotaxis of various inflammatory cytokines after specific individual contact with antigen. The nasal mucosa produces various pathological changes, and the excitability of the nasal parasympathetic nerve is too strong, resulting in vascular dilation, enhanced permeability, excessive secretion of serous cells,^[23]^ modern medicine is mainly based on drug treatment, Medications include oral and topical histamine H1 receptor antagonists, topical and systemic glucocorticosteroids, chromones, decongestants, topical anticholinergics, antileukotrienes, and oral anti-allergic drugs.^[24]^ However, the adverse reactions caused by it are still a common concern of doctors and patients, and the curative effect is limited, unable to completely relieve the symptoms^[25]^ Therefore, it is necessary to find alternative treatment options for patients with allergic rhinitis.

Ear acupuncture has the characteristics of simple operation, less pain, less side effects and lasting and stable effect. Clinical studies have proved that lung (CO_14_) and wind stream (SF_1,2i_) can relieve congestion and runny nose, adrenal gland (TG_2p_) can resist inflammation and allergy, and its mechanism of action may be to regulate the imbalance of Th1/Th2 cells by inhibiting the differentiation of Th cells to Th2, thereby reducing the synthesis of IgE and inhibiting the occurrence of allergic reactions.^[26]^ Although EAP has been widely used in the treatment of allergic rhinitis in China, there is still a lack of strict clinical studies to verify its curative effect. The existing clinical studies mostly use EAP combined with other treatment schemes, or compare the curative effect with western medicine, and many confounding factors interfere with our evaluation of its curative effect.^[27,28]^ Therefore, we designed this randomized controlled study to determine the efficacy of EAP in the treatment of allergic rhinitis by comparing with sham EAP.

In addition, there are still some deficiencies in the design of this study. First of all, due to the limited treatment methods, this study cannot carry out double-blind design, which may lead to certain bias. Second, this study is a single-center study, and the source of the case is relatively single and limited, which may affect the conclusions of the study to some extent.
